## Methods

### Design

The study design is a parallel, randomized controlled trial (RCT) with the following 3 study arms: (1) an experimental group receiving an 8-week, fully automated, computer-tailored, Web-based intervention; (2) an experimental group receiving an 8-week, peer support, Web-based intervention; and (3) a control group that does not receive any intervention during the study period. A baseline measurement (T0) and two follow-up measurements at three (T1) and nine (T2) months after baseline are included. All three arms follow the same study timeline and are invited to complete the assessments during the same period. The protocol was developed in accordance with the CONSORT-EHEALTH checklist [70] and the SPIRIT statement 2013 [71].

### Eligibility and Recruitment

The target population for this research project is Canadian men and women with self-reported T2D residing in the province of Quebec. Other inclusion criteria to be eligible for the research project are not meeting the Canadian Diabetes Association guidelines on moderate-intensity aerobic PA [72], being able to understand French, having access to the Internet, being between 18 and 65 years of age, and not having medical indications limiting the practice of PA. Eligibility was evaluated with a self-reported questionnaire administered to potential participants via the intervention websites during the study registration process.

As for the recruitment process, the research project was implemented in partnership with Diabète Québec, a recognized association for people with T2D in the province of Québec, Canada. Following a joint agreement between both parties, Diabète Québec sent 2 invitation emails over a 2-week period (from 2014 September 15 to 28) to all Canadian Francophones with T2D meeting the age criteria and who subscribed to the association’s newsletter.

### Randomization

Two websites were created for this study: one to host activities related to the computer-tailored intervention, and the other to host activities for the peer support intervention and those of the control group. Randomization with a 1:1:1 allocation ratio was performed in three steps. First, all Diabète Québec newsletter recipients with T2D who were between 18 and 65 years of age received invitation emails to participate in the study, resulting in 6425 potential participants. Next, 35% of these 6425 potential participants were randomly sampled by Diabète Québec via a computer algorithm to receive emails with a URL link redirecting them to the first website (computer tailoring group). Meanwhile, the remaining 65% of potential participants received emails giving them access to a URL redirecting them to the second website. Finally, potential participants who had been redirected to the second website were then allocated randomly by the web solution company responsible for the website development to either the peer support intervention group or the control group via a computer algorithm. The randomization procedures mentioned above were conducted independently of the research team. This is an open-label RCT, meaning that participants and investigators know who has received which intervention.

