**Methods:**

A 3-arm, parallel randomized controlled trial with 2 experimental groups and 1 control group was conducted in the province of Quebec, Canada. A total of 234 participants were randomized at a 1:1:1 ratio to receive an 8-week, fully automated, computer-tailored, Web-based intervention (experimental group 1); an 8-week peer support (ie, Facebook group) Web-based intervention (experimental group 2); or no intervention (control group) during the study period.

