### Additional Features

Despite their distinct core content, both interventions possessed the following similar features: (1) the appearance of the website home page, (2) a tool for self-monitoring of PA behavior, (3) tools for goal setting and action planning, (4) tabs providing safety tips on how to practice PA properly, and (5) access to technical support via email. The designs of the websites were different except for the home page (see Multimedia Appendix 4), as they were developed by different web solution companies at different times during the study development phase. Additionally, other evidence-based behavior change techniques according to Michie et al’s taxonomy [89] were integrated into both interventions and can be viewed in detail in Multimedia Appendix 5 [90-96]. These were identified in the literature review preceding the development of both interventions [80]. Lastly, the computer-tailored and peer support interventions both started on 29 September 2014 and ended on 22 November 2014.

Table 1 presents a broad overview of the intervention components for each experimental condition. Multimedia Appendix 2 presents a more detailed overview of both interventions, including timelines.

**Table 1 table1:** Overview of components found in each intervention group and the control group

		Study groups		
		Computer-tailored intervention	Peer support intervention	Control group

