### Ethics Approval and Participant Consent

Ethics approval was obtained from the Ethics Committee of Research with Humans from the Université du Québec à Trois-Rivières on 2014 September 12 (CER–13–194–08.03.04). All participants in the study gave their informed consent online via the study websites during the registration process.

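### The 1:1:1 randomization of 234 participants is misdescribed: 6,425 invitees were split 35:65 before eligibility and consent, so H1 and H3 are open to selection after allocation

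*Protocol article*

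**What the plan says.** The abstract states: "A total of 234 participants were randomized at a 1:1:1 ratio". The Randomization section repeats the ratio: "Randomization with a 1:1:1 allocation ratio was performed in three steps". It then sets out the steps.

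- **Invitation.** Newsletter recipients with type 2 diabetes in the age range "received invitation emails to participate in the study, resulting in 6425 potential participants".
- **First random step.** "35% of these 6425 potential participants were randomly sampled" by the partner association with a computer algorithm, and emailed a link to the computer-tailoring site. The remaining 65% were emailed a link to a second site.
- **Second random step.** People directed to the second site were allocated at random to peer support or control. The section gives neither the ratio of this step nor its timing relative to eligibility and consent, and it calls the people allocated potential participants.

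Two other sections fix the order of events. Eligibility and Recruitment says: "Eligibility was evaluated with a self-reported questionnaire administered to potential participants via the intervention websites during the study registration process". Ethics Approval and Participant Consent says that participants "gave their informed consent online via the study websites during the registration process". Additional Features adds: "The designs of the websites were different except for the home page".

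The Statistical Analysis section compares all three arms in one linear mixed model. It adjusts for sociodemographic and other relevant variables that differ significantly between arms at baseline. The limitations in the Discussion cover open-label performance bias, self-report and attrition, but not selection after allocation.

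**The concern.** The unit and the timing of randomization decide which comparison it protects. The first step randomized invitees. A comparison of all 6,425 by link sent would be fully protected, but the trial analyses the few who went on to register, qualify and consent. No later step places an enrolled person in or out of the computer-tailored arm.

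If the two links drew different people into the trial, the computer-tailored arm could differ from the other two before any intervention began. H1 (tailoring versus control) and H3 (tailoring versus peer support) both cross that boundary. H1 is one of the two hypotheses under the primary aim. A reader told that 234 participants were randomized 1:1:1 would credit these contrasts with a protection that the described procedure gives only in part.

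**Working it through.** **Inputs.** From Randomization: 6,425 invitees, split 35% and 65%. From Sample Size Calculation: 234 enrolled at baseline. Assumed, because not stated: an equal split between peer support and control on the second site.

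**Order of events.** The emails carried the result of the first split. Eligibility and consent took place during registration on the site that the link opened. Both therefore came after allocation to or away from computer tailoring.

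**Invitees by link.**
- First site: 0.35 × 6,425 = 2,248.75, about 2,249.
- Second site: 0.65 × 6,425 = 4,176.25, about 4,176. Under the assumed equal split this is about 2,088 per arm.
- The ratio among invitees is then 35:32.5:32.5.

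**Enrolment.** 234 / 6,425 = 3.64%, so about 96.4% of those split by link are not in the analysed sample.

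**Expected arm sizes with the same enrolment rate on both sites.**
- Tailoring: 0.35 × 234 = 81.9.
- Peer support and control: 0.325 × 234 = 76.05 each.
- So about 82:76:76. The 95% binomial range for the tailoring arm, given 234 enrolled and probability 0.35, is 68 to 96. An arm of 78 lies well inside it.

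**If enrolment differs by link.** Let r be the enrolment rate on the first site divided by that on the second. The tailoring share is 0.35r / (0.35r + 0.65). The article does not report r, so these values are illustrative:

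| r | Tailoring | Peer support | Control |
|---|---|---|---|
| 0.8 | 70 | 82 | 82 |
| 1.0 | 82 | 76 | 76 |
| 1.25 | 94 | 70 | 70 |
| 1.5 | 105 | 65 | 65 |

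The enrolled ratio thus depends on behaviour after allocation. Randomizing 1:1:1 after consent would give an expected 78:78:78 whatever the enrolment rates.

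**Would the adjustment rule catch an imbalance?** Take 234 / 3 = 78 per arm, a two-sided 5% test of a baseline variable between two arms, and a true imbalance of d SD. The standard error is √(2/78) = 0.160 SD, and the chance of a significant result is about 1 − Φ(1.96 − d/0.160), ignoring the negligible opposite tail.
- d = 0.2: d/0.160 = 1.25, chance about 24%.
- d = 0.3: d/0.160 = 1.87, chance about 47%.
- d = 0.4: d/0.160 = 2.50, chance about 70%.

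A three-arm F test with only the tailoring arm shifted by 0.3 SD does no better. Its noncentrality is 0.3² / (1/78 + 1/156) = 4.68 on 2 and 231 degrees of freedom, which again gives about 47%. The values of d are assumptions, since the article reports no baseline data by arm.

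**The case against.** The strongest reply is that the first split was itself random. A computer algorithm drew it, independently of the research team, so bias needs enrolment that differs by link. The only difference described between the emails is the URL. The home pages looked alike, and the Discussion says participants did not know the hypotheses and were told only that different Web-based interventions were being assessed. The open-label statement does not say that invitees knew their arm before consenting. All of this stands: it makes strong differential selection less likely, though it does not restore randomization among those enrolled.

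It is also fair that the plan already adjusts for baseline differences, and that a trait shifting activity equally at all three time points drops out of the time × group interaction. The first is partial cover, as the working shows, and cannot reach unmeasured selection. The second means that no size of bias in the planned interaction test can be derived from the article. Traits that predict change could still bias that test, and post-hoc comparisons of raw means could also be affected.

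Three stronger readings are tempting, and the article does not support them.
- **That H1 and H3 are biased or not randomized at all.** Differential enrolment is shown to be possible, not to have occurred.
- **That website is fully confounded with arm.** Peer support and control share a site, and for computer tailoring the site is the means of delivering the intervention.
- **That H2 is untouched.** This holds only if the second allocation followed eligibility and consent, and the article does not say so.

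**Conclusion.** The statement that 234 participants were randomized 1:1:1 is wrong as written. The article describes a random 35:65 split of 6,425 invitees before eligibility and consent, followed by a random allocation on the second site only. The protection of randomization is weakened for H1 and H3, and the limitations do not say so. The status of H2 is open until the timing of its allocation is stated.

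The departure in the ratio is minor, and its exact size rests on the assumed equal second split. What matters is the timing, together with an enrolment of 3.6%. That low rate alone limits generalisability; it threatens H1 and H3 only if selection differed by link. Confidence is high on the order of events. The article gives no evidence on whether bias arose or how large it would be.

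**What to change.** Enrolment is complete and analysis is under way, so the changes concern reporting and the model.

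1. Replace the 1:1:1 wording, and the claim that 234 were randomized, with the actual two-stage process. State the ratio of the second-site allocation and whether it came before or after eligibility and consent.
2. Report the numbers invited, registered, eligible, consented and enrolled, by link.
3. Replace covariate selection by baseline significance with a fixed set of prognostic covariates that is always included, for example age, sex, education, body mass index and intention, with baseline activity accounted for in the model.
4. List selection after allocation as a limitation. Word the H1 and H3 conclusions as conditional on comparable enrollees across the two links, and do the same for H2 if its allocation preceded consent.

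A propensity-weighted sensitivity analysis is optional. It would use much the same measured covariates and cannot address unmeasured selection.

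The cost is small: revised wording, recruitment counts to be drawn from the partner association and the two websites, and a changed covariate list. The claims for H1 and H3 become slightly more modest.

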### Sample Size Calculation

Calculation of the sample size was achieved with GPower 3.0.10, and instructions for selecting different criteria were taken from Erdfelder et al [73]. Thus, according to a mixed-plan, 3 (2 experimental groups and 1 control group) x 3 (baseline and 3- and 9-month follow-ups) design, assuming a statistical power of .80 and an alpha value of .05, a total sample size of 204 participants is necessary to detect a conservative effect size of d=.20 [74]. This effect size was chosen with reference to results observed in the field of computer-tailored interventions [33,75] and considering the modest evidence observed to date for Web-based interventions integrating online opportunities for peer support [25,76]. Moreover, to obtain the calculated sample size at the end of the study (N=204), it was estimated that at least 6000 participants needed to be solicited through the invitation emails sent by Diabète Québec. This estimate was based on a similar study [77], and a review of additional literature: (1) from the 6000 participants solicited, 30% (1800/6000) will agree to participate in the study [77,78]; (2) of this number, almost 100% (1800/1800) will have T2D, since preselection of potential participants with this type of diabetes will be executed by Diabète Québec; (3) 85% (1530/1800) will not have medical indications limiting the practice of moderate-intensity aerobic PA [79]; (4) 70% (1071/1530) will not meet the Canadian Diabetes Association guidelines related to aerobic PA [77]; (5) 70% (749/1071) will have access to the Internet [15]; and (6) 60% (449/749) will complete the study [77]. However, this algorithm has overestimated the number of participants enrolled at baseline, which was 234.

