### Aim of the Study and Hypotheses

The primary aim of this study is to evaluate the independent effectiveness of two Web-based interventions in promoting regular moderate-intensity aerobic PA among insufficiently active adult Canadian Francophones with T2D. In line with this aim, it is hypothesized that the Web-based computer-tailored intervention (H1) and the Web-based peer support intervention (H2) will be more effective at increasing moderate-intensity aerobic PA levels compared to a control group at 3 and 9 months after baseline. Another aim of this study is to compare the relative effectiveness of the two Web-based interventions at increasing moderate-intensity aerobic PA levels. Hence, the third hypothesis is that participants in both intervention groups will show a different level of moderate-intensity aerobic PA at 3 and 9 months after baseline. This hypothesis is formulated bilaterally, because no study to date has compared these two methods.

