### Statistical Analysis

Descriptive statistics will be used to summarize the baseline characteristics of the participants for sociodemographic variables (ie, origin, occupation, gender, age, and education), anthropometric variables (ie, height, weight, and body mass index), psychosocial variables (ie, attitude, social influence, self-efficacy, type of motivation, and intention), and PA level. In line with the hypotheses, linear mixed model analyses for repeated measures will be used to examine the effectiveness of the computer-tailored intervention (H1) and peer support intervention (H2) relative to the control group and also to compare both interventions to each other (H3). A linear mixed-model approach is very well suited for modelling data containing repeated measures from several participants [103] and has the advantage of providing better capabilities for handling missing observations when data are missing at random, compared to more traditional approaches such as repeated measures analysis of variance [104,105]. In accordance with the statistical procedure and for each analysis, group, time, and time × group will be included as independent variables and minutes per week of moderate-intensity aerobic PA will be included as the dependent variable. Analyses will be adjusted for sociodemographic characteristics and other relevant variables that significantly differ between the 3 study arms at baseline. In the presence of statistically significant interaction terms, post-hoc tests will be applied to compare differences between all pairs of means. All pairwise tests of the computer-tailored or peer support interventions compared to the control group will be 1-tailed, and tests comparing both interventions together will be 2-tailed. Finally, potential mediators of the interventions’ effects will be explored. Based on the theoretical framework (Figure 1), a mediation analysis will be conducted involving a multicategorical independent variable (both interventions relative to control group), with type of motivation and intention as mediator variables in serial, and PA behavior as the dependent variable. Hayes and Preacher’s SPSS macro will be used for exploring the potential mediators [106]. The statistical analyses will be conducted with SPSS 22.0.

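### A total of 204 participants does not give 80% power for a between-arm difference of d=.20; the figure fits a different and larger effect, and power for d=.20 is well below 80%

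*Protocol article*

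**What the plan says.** In the section Sample Size Calculation, the article reports: "Calculation of the sample size was achieved with GPower 3.0.10". The design entered is a "3 (2 experimental groups and 1 control group) x 3 (baseline and 3- and 9-month follow-ups) design". Power is set at 80% and alpha at 5%, and the conclusion is that "a total sample size of 204 participants is necessary to detect a conservative effect size of d=.20". On where the effect came from: "This effect size was chosen with reference to results observed in the field of computer-tailored interventions". It is therefore presented as the size of treatment effect the trial can detect. The section does not say which effect was tested, what f was entered, or what correlation and sphericity were assumed.

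The hypotheses are comparisons between arms. Under Aim of the Study and Hypotheses, each intervention "will be more effective at increasing moderate-intensity aerobic PA levels compared to a control group at 3 and 9 months after baseline" (H1 and H2), and the two interventions are expected to differ from each other (H3). Under Statistical Analysis, "All pairwise tests of the computer-tailored or peer support interventions compared to the control group will be 1-tailed", while the comparison of the two interventions is two-tailed. The same section makes the pairwise tests conditional on a significant interaction.

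**The concern.** A d of .20 drawn from intervention studies reads naturally as a 0.20 SD difference between an intervention arm and its comparator. With 204 in three equal arms there are 68 per arm, which is small for that effect. An ordinary two-group comparison at one time point would need about 310 per arm (one-tailed) or 393 per arm (two-tailed). The repeated-measures design would have to make up a very large gap.

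If it does not, readers may credit the trial with a sensitivity it lacks. A nonsignificant result could be taken as evidence against a 0.20 SD effect that the trial would probably miss. The Discussion also suggests that the results may indicate which of the two approaches to prioritize, and that rests on H3. It lists low recruitment and attrition as limitations, but not that 204 itself falls short of the stated aim.

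**Working it through.** **Inputs from the article.** k=3 groups, m=3 measurements, alpha .05, power .80, d=.20, N=204 (68 per arm at 1:1:1), H1 and H2 one-tailed, H3 two-tailed. **Inputs assumed.** The correlation ρ between repeated measures is varied, and sphericity is taken to hold. The only related figure in the article is the one-month test-retest reliability of .62 for the activity questionnaire, an imperfect proxy over 3 to 9 months.

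**1. Reproducing 204.** For the interaction, λ = f²·N·m/(1−ρ), with df (k−1)(m−1) = 4 and (N−k)(m−1). With f=.10 and ρ=.5:
- N=204: λ = .01 × 204 × 3/.5 = 12.24, df 4 and 402, power .806.
- N=201: power .799.

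So 204 is the smallest total divisible by three. There is a second route. For the between-groups effect, λ = f²·N·m/(1+(m−1)ρ). With f=.20 and ρ=.75, λ = .04 × 204 × 3/2.5 = 9.79, and power is .801 at 204 against .794 at 201. Neither f is a between-arm d of .20.

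**2. Interaction f for a between-arm d of .20.** Take no difference at baseline. If both interventions differ from control by d at both follow-ups, the arm pattern is (1,1,0) and the time pattern is (0,1,1). Each has SD √(2/9) = .471, so f = d × 2/9 = .20 × .222 = .044. The value is the same if only one intervention works. Conversely, f=.10 corresponds to .10/.222 = 0.45 SD.

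If one intervention has half the effect of the other, or the effect halves by 9 months, one pattern becomes (1, ½, 0) in some order, with SD √(1/6) = .408. Then f = .20 × .408 × .471 = .038, and f=.10 corresponds to .10/.192 = 0.52 SD.

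**3. Interaction power at N=204 for d=.20.**

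| ρ | sustained (f=.044) | one arm halved, or fading (f=.038) |
|---|---|---|
| .3 | .15 | .12 |
| .5 | .20 | .16 |
| .62 | .26 | .20 |
| .7 | .32 | .24 |

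At ρ=.5 the sustained pattern would need about 1,011 participants for 80%. At 204 it reaches 80% only at ρ of about .90. Using all 234 enrolled gives about .22 at ρ=.5.

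**4. Pairwise contrasts at one time point, 68 per arm, with no precondition.** The noncentrality is d·√(n/2)/s = .20 × √34/s = 1.166/s, with s=1 unadjusted and s=√(1−ρ²) adjusted for baseline.

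| | one-tailed (H1, H2) | two-tailed (H3) |
|---|---|---|
| unadjusted | .31 | .21 |
| adjusted, ρ=.5 | .38 | .27 |
| adjusted, ρ=.62 | .43 | .31 |
| adjusted, ρ=.7 | .49 | .37 |

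Averaging both follow-ups with baseline adjustment at ρ=.5 gives roughly .50 one-tailed and .38 two-tailed.

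**5. The planned sequence.** A pairwise test follows only a significant interaction. The chance that both are significant cannot exceed the chance that the interaction is. Read as the overall interaction test, this limits the step 4 figures to those in step 3.

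**The case against.** A reader might infer that the plan converted d to f by halving it, which is valid for two group means, and that this is the established source of the error. The documents do not support that as fact. They give neither f nor the correlation, and step 1 shows a second route to 204, under which an f of .20 would have been labelled d. The interaction route is likelier, but it remains an inference. The conclusion does not need it, because power for d=.20 can be computed at N=204 whatever was entered.

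A reader might also settle on 20-38% as the real power. That range holds only at a correlation of .5, which the article does not state, and it mixes the interaction with one- and two-tailed contrasts. Higher correlations or averaging the follow-ups raise the contrast figures, while the planned sequence pulls them down. The 0.45 SD equivalent likewise assumes a sustained effect, and it becomes 0.52 SD under the other patterns in step 2.

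It is fair to add that nothing in the article says a null result will be read as excluding 0.20 SD, that the Discussion admits low recruitment, and that a condensed article may leave the assumed correlation to the full protocol. What these points do not do is rescue the sentence. No plausible correlation brings power for a between-arm d of .20 to 80% at 204: the interaction needs about .90, against a one-month reliability of .62.

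**Conclusion.** The statement is wrong if d is a between-arm standardized difference, which is how its source and the hypotheses present it. The total of 204 fits 80% power for f=.10 on the interaction at correlation .5, an effect more than twice as large: about 0.45 SD sustained, or about 0.52 SD if one arm has half the effect or the effect halves by 9 months. For d=.20, interaction power is about 15-32% over correlations .3 to .7 when the effect is sustained, and 12-24% under those weaker patterns. Single-time-point contrasts taken alone have about 31-49% (H1, H2) and 21-37% (H3), from unadjusted to baseline-adjusted at correlation .7. Under the planned sequence they cannot exceed the interaction power.

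These figures assume sphericity, equal arms, no loss to follow-up and no baseline difference. They use repeated-measures analysis of variance as a stand-in for the planned mixed model. The shortfall is firm; its exact size depends on the correlation and the effect pattern.

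**What to change.** Replace the sentence with what 204 supports: 80% power for f=.10 on the time x group interaction, assuming a correlation of .5 and sphericity. Give its equivalent as about 0.45 SD if sustained at both follow-ups, and about 0.52 SD if one intervention has half the effect or the effect halves by 9 months. First confirm from the saved calculation that this was the route taken; if it was not, state the inputs actually used.

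Add that power for a between-arm d of .20 is well below 80%. Show it as a range over correlation and effect pattern with each assumption labelled, and note that the pairwise tests are limited by the preceding interaction test. In the results report, interpret nonsignificant comparisons through confidence intervals, not as evidence of no effect.

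The cost is wording only. No participants, endpoints, models or tests change, but the stated sensitivity becomes less favourable.

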However, this study is not without limitations. First, given its open-label design (ie, not blinded), although quite common in Web-based interventions delivered under free-living conditions [110], participants in all 3 study groups and researchers were aware of the participants’ group assignment. This has the potential to introduce performance bias, defined as “systematic differences between groups in the care that is provided, or in exposure to factors other than the interventions of interest” [120]. All participants were, however, unaware of the hypotheses of the study and were only told that the researchers wanted to assess the effect of different Web-based interventions on PA behavior in adults with T2D. Second, given the use of self-reported measures for the outcome assessments, even from validated questionnaire items, this has the potential to introduce detection bias, defined as **“**systematic differences between groups in how outcomes are determined**”** [120]**.** However, outcome data assessment was automated through the study websites and was thus blinded to the research team, which should reduce the possibility of a differential bias between intervention groups and the control group. Furthermore, the third hypothesis regarding the comparative effectiveness of the interventions was formulated bilaterally, reducing the possibility of bias on the investigators’ part. Finally, one possible limitation across Web-based interventions is the attrition phenomenon [97,121]. Despite a smaller than expected number of participants recruited at baseline and the impossibility of fully preventing a high attrition rate, some evidence demonstrated that adding personalization, computer tailoring, and peer support components could contribute to reducing the attrition rate in Web-based interventions [110,121]. Financial compensation associated with follow-up completion might also have helped reduce the attrition rate of our study [122].

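### The sample size target is 204 at study end with 60% completion assumed, but the 234 enrolled are not converted into expected completers (about 140) and the power of .80 is not restated

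*Protocol article*

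**What the plan says.** Under Sample Size Calculation, the protocol article sets out its layout as a "3 (2 experimental groups and 1 control group) x 3 (baseline and 3- and 9-month follow-ups) design". The error rates behind the calculation are given as "assuming a statistical power of .80 and an alpha value of .05", and the section concludes that "a total sample size of 204 participants is necessary to detect a conservative effect size of d=.20". It makes clear when those 204 are needed; the recruitment funnel is built "to obtain the calculated sample size at the end of the study (N=204". The funnel starts from 6000 invitations, reaches 749 eligible participants with Internet access, and ends with the assumption that "60% (449/749) will complete the study".

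The section closes with the outcome of recruitment: "However, this algorithm has overestimated the number of participants enrolled at baseline, which was 234". The abstract gives the same count: "A total of 234 participants were randomized at a 1:1:1 ratio". The limitations paragraph of the Discussion returns to it ("Despite a smaller than expected number of participants recruited at baseline"), concedes that high attrition cannot be fully prevented, and gives reasons why tailoring, peer support and payment might reduce it. No section gives an expected number of completers, a revised power or a detectable effect for the 234.

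**The concern.** The target of 204 counts people at the end of follow-up, whereas 234 counts people at the start. The two differ by the attrition that the same paragraph puts at 40%. Set side by side without that step, 234 looks larger than 204. The comparable funnel figure before attrition is 749, and 234 is 31% of it (234/749).

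What is at stake is how a null or uncertain result will be read. The only power figure in the article is .80. The trial is meant to show whether each intervention beats control and whether the two differ. A reader who judges a non-significant result against .80 would give it more weight than the plan's own completion rate supports.

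**Working it through.** **Inputs from the article (Sample Size Calculation).** Three groups, three time points, alpha .05, power .80, d=.20, N=204 at study end, 60% completion, 234 enrolled.

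**Inputs inferred, not stated.** The article does not name the effect tested, the conversion from d to f, or the within-person correlation. I take the group-by-time interaction, f = d/2 = .10, correlation .5 and sphericity.

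**1. Reproduce 204.** For the repeated-measures interaction with k=3 groups and m=3 times:

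- noncentrality λ = f²·N·m/(1−ρ)
- df1 = (k−1)(m−1) = 4
- df2 = (N−k)(m−1)

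At N=204, λ = .01×204×3/.5 = 12.24, df2 = 402 and power is .806. At N=201 power is .799. So 204 is the smallest total divisible by three that reaches .80, which matches the article exactly.

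**2. Apply the plan's completion rate.**

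- Expected completers: 234 × .60 = 140.4, about 140 (about 47 per arm)
- Shortfall: 204 − 140 = 64, or 31% of 204
- Enrolment needed for 204 completers: 204/.60 = 340
- Completion needed from 234: 204/234 = 87.2%

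None of these four figures depends on the inferred inputs.

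**3. Power on completers, same formula.**

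| N analysed | λ | df2 | Power |
|---|---|---|---|
| 140 (60% of 234) | 8.40 | 274 | .62 |
| 204 (target) | 12.24 | 402 | .81 |
| 234 (no attrition) | 14.04 | 462 | .86 |

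*Does the inferred correlation drive the .62?* No. Another setting that yields 204 is f=.141 with correlation 0. It has the same noncentrality per participant (.02×3/1 = .06, against .01×3/.5 = .06), so power at 140 is again .62. A between-group test with f=.20 and correlation about .74 also yields 204 and gives a similar figure at 140 (.62 to .63).

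**4. Power for the planned mixed model.** Under Statistical Analysis, the article plans a linear mixed model, which also uses partial data. I took 234 enrolled in equal arms, compound symmetry with correlation .5, dropout missing at random and the interaction scaled to f=.10. Information was summed over three patterns: complete, through 3 months only, and baseline only. Six mean patterns were tried (for example, a gain held from 3 to 9 months, a linear gain, a gain at 9 months only). Retention at 9 months was held at 60%.

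| Retention at 3 months | Power across mean patterns |
|---|---|
| 60% | .64 to .69 |
| 70% | .64 to .74 |
| 80% | .64 to .79 |
| 100% | .65 to .86 |

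Power exceeds .80 only in the last row, and there only for some patterns. It does not for the linear gain (.72) or the gain at 9 months only (.65).

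**5. Pairwise contrasts, completers only (supplementary).** With 47 per arm, detectable difference = (z₁₋α + z.₈₀)·√(2v/47) in SD units. Here v=1 is an unadjusted comparison and v=.75 allows for baseline with correlation .5.

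- One-tailed, each intervention against control: (1.645+.842)×√(2/47) = .51; with v=.75, .44
- Two-tailed, intervention against intervention: (1.960+.842)×√(2/47) = .58; with v=.75, .50

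The variance factors are assumptions, and the 204 was not derived from these contrasts.

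**The case against.** The strongest reply is that the article makes no false statement. The .80 is an input to the calculation of 204, and no sentence claims it for the 234. The closing sentence of the sample size section signals a shortfall, and the Discussion lists both low recruitment and attrition as limitations. Every step of the funnel computes. The 60% is a forecast borrowed from a similar study, final completion is not reported, and incentives were offered to improve it. The planned mixed model also recovers information from people who drop out, so a completer-only power understates the analysis.

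Most of this stands, and it sets the limits of the point. A reader might infer that the article claims 80% power for the enrolled sample, or that the trial has definitely missed its power and has only .62. The documents support neither. The 140 is what the plan's own forecast implies and not an observed count; .62 is a completer-only floor; and the inputs behind it are inferred. Nor is this an arithmetic slip, since an observed enrolment fell below a forecast.

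What does not stand is that disclosure settles the matter. The article reports the shortfall and then stops before its consequence, although every figure needed is in the same paragraph. The mixed model softens the loss but does not remove it at the assumed completion rate, except in some patterns with nearly complete 3-month follow-up.

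**Conclusion.** The point holds as an uncorrected planning figure. At the article's own 60%, 234 enrolled means about 140 completers against a requirement of 204, a gap of 64. On the article's completer-based reckoning, .80 is not expected to hold unless completion reaches about 87%.

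The counts rest only on stated figures. The power figures (about .62 on completers, roughly .64 to .79 for the planned mixed model with 60-80% retention at 3 months and 60% at 9 months, .86 with no attrition) rest on an interaction test with f=.10 and correlation .5. Those inputs are inferred because they reproduce 204. The mixed-model range further assumes compound symmetry and data missing at random. It affects how results are interpreted and does not invalidate the design or the analysis.

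**What to change.** After the 234 figure under Sample Size Calculation, add one paragraph that:

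- states that about 140 completers are expected at 60% completion, against the 204 required, and that on a completer basis .80 is not expected to hold unless completion reaches about 87%;
- gives power as a range: about .62 (completers only, 60%), roughly .64 to .79 (planned mixed model, 60-80% retained at 3 months and 60% at 9 months) and .86 (no attrition);
- states the test, effect size f and correlation actually entered in the software, or labels those used here as inferred.

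Detectable pairwise differences (about 0.44 to 0.51 SD one-tailed, 0.50 to 0.58 SD two-tailed at 47 per arm) may be added, but only as completer-based figures with the variance assumptions stated. A cross-reference in the limitations paragraph of the Discussion would help.

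The cost is a paragraph of text. It requires no extra enrolment and no change to the hypotheses or the analysis.
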